### Sample size

A total sample size of 1,500 participants (n = 500 per arm) will have at least 80% power (alpha = 0.05) to detect a minimum 2-unit difference in the mean nutrient profiling score between either of the intervention arms and control with adjustment for multiple comparisons. A 2-unit change in nutrient profiling score is approximately equivalent to the following changes in nutrient content per 100 g food: 78 kJ energy, 0.95 g saturated fat, 1.5 g total sugars and 73 mg sodium (unpublished data). The nutrient profile score will be estimated using the FSANZ nutrient profiling scoring calculator, where food scores span a range of -17 to 53 (a lower score is healthier) [28]. The power estimate assumes a standard deviation of 9.9 based on distribution of >25,000 foods in an Australian food database.

### Statistical analyses

Statistical analyses will be performed using SAS version 9.3 (SAS Institute Inc. Cary NC). All statistical tests will be two-tailed and maintained at a 5% significance level. The baseline characteristics of all study participants will be summarised and tabulated using means (standard deviations, medians and ranges) and frequencies (proportions). Analysis of covariance (ANCOVA) regression models will be used to compare mean nutrient profiling score between intervention and control groups, adjusting for baseline nutrient profiling score and stratification factors. A similar approach will be used for continuous secondary outcomes. Generalized linear models will be used for secondary categorical outcomes. No imputation will be undertaken. Repeated measures mixed models will be used to evaluate treatment effects over time. Sub-group analyses will test possible interactions of the labelling intervention with key food categories, ethnicity (Maori, Pacific, Other), income tertile, and baseline self-reported interest in “healthy eating”. Sensitivity analyses will be undertaken using data only from participants who return at least 75% of till receipts/food purchase data based on pre-randomisation usual reported number of shopping episodes. A statistical analysis plan will be prepared by the trial statistician prior to the final data lock. Reporting will adhere to the CONSORT 2010 guidelines for reporting parallel group randomised trials.

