### Study population

The Starlight trial will recruit 1500 New Zealand adults (aged 18 years and older) who have a smartphone (iPhone or Android), are main household shoppers (i.e. complete 50% or more of the grocery shopping for their household), and shop at a supermarket at least once a week. Participants must be able to read and understand English, and be available for the full duration of the 5-week trial. Only one person per household can participate in the study. Current or previous FoodSwitch app users will be excluded, because FoodSwitch provides TL labels and recommends healthier food options.

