### Randomisation

Participants who complete the run-in phase successfully will be randomised in a 1:1:1 ratio to one of the three label formats (TL; HSR or NIP), using a central computer-based randomisation system. Blocked randomisation will be used with variable block sizes, stratified by self-identified ethnic group (Māori, Pacific, Other) and self-reported interest in “healthy eating” (not particularly interested; moderately to very interested).

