### Data collection

The baseline questionnaire will collect demographic details (age, gender, ethnicity, income, education level, family size) and self-reported information on interest in nutrition and healthy eating.

Data on participant food and beverage purchases will be collected throughout the one-week baseline and four-week intervention period. Usage of the labelling function will be automatically recorded by the “Food Label Trial” app. Objective purchase data will be supplied by participants in the following modes: 1) electronic list of scanned purchased items (“Food Label Trial” app function); 2) photographs of corresponding grocery till receipts (“Food Label Trial” app function); 3) hard copies of grocery till receipts (returned by participants at the end of the intervention period). The electronic lists of purchased items will be used as the primary data source of packaged food purchases. The till receipts provide information on price and on purchases of non-barcoded items. Photographs of till receipts will be used as a back-up for missing hard copy till receipts.

All data collected via the “Food Label Trial” will be automatically transmitted via Wi-Fi or 3/4G to the app database, hosted on a remote server, and subsequently extracted by researchers to the study database. Hard copies of till receipts will be mailed by participants to the study centre and the additional data manually entered into the study database.

A follow up questionnaire will collect participant feedback on the app (technical issues, usefulness, self-reported impact on food choices), self-reported compliance with the trial protocol (number of shopping events recorded and till receipts returned, usage of the trial app) and perceived changes in participant’s nutrition knowledge.

Regular reminder messages (3 times per week) will be sent throughout the intervention period to encourage participants to use the app and submit data, and to minimise attrition. At the end of the study participants will be provided with reward vouchers as a compensation for the time and potential costs associated with taking part in the trial.

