### Outcomes

The primary outcome of the trial will be the mean nutrient profiling score for all food and beverage products purchased over the four-week intervention period. Nutrient profiling score will be calculated using the Food Standards Australia New Zealand (FSANZ) nutrient profiling standard [26]. Food composition data will be obtained from Nutritrack, a brand-specific processed food composition database that contains comprehensive annually-updated information on New Zealand packaged and fast foods [27]. As a secondary approach, the crude nutrient profiling score will be transformed to a scale of 0–100 consistent across all 3 NPSC category foods. A tertiary approach will also be considered on weighted nutrient profiling score stratified by key food categories.

Secondary outcomes will be the difference between trial arms in:Mean saturated fat, total sugar, sodium and energy content per 100 g food purchases over the four-week intervention period;Mean weekly food expenditure over the four-week intervention period;Labelling profile of food purchases (mean number of HSR stars and proportions of red, green and amber traffic lights) over the four-week intervention period;Mean nutrient profiling score for all food and beverage products purchased each week of the intervention period;Mean nutrient profiling score of key food categories likely to be most impacted by nutrition labelling (e.g. breakfast cereals, cereal bars, pizzas and ready meals);Mean nutrient profiling score of the 3 nutrient profiling score criterion food categories (beverages, fats and oils, all other foods)Mean purchases of unpackaged foods (e.g. fruit and vegetables) in g/100 g;Self-reported nutrition knowledge at follow-up;Use of assigned labelling system as recorded by the Food Label Trial app.

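### Naming family size as a covariate in the food-expenditure model would give a modest, nearly free gain in precision

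*Protocol article*

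**What the plan says.** All references are to the Protocol article.

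- **Outcomes** lists "Mean weekly food expenditure over the four-week intervention period" as a secondary outcome. No scaling per person is stated, whereas the nutrient outcomes are expressed per 100 g.
- **Study population** recruits main shoppers, defined as those who "complete 50% or more of the grocery shopping for their household".
- **Data collection** says the baseline questionnaire covers "demographic details (age, gender, ethnicity, income, education level, family size" and interest in nutrition and healthy eating. It also sets the measurement window: "Data on participant food and beverage purchases will be collected throughout the one-week baseline and four-week intervention period".
- **Randomisation** is "stratified by self-identified ethnic group (Māori, Pacific, Other) and self-reported interest in “healthy eating". Family size is not a stratum.
- **Statistical analyses** specifies the primary ANCOVA as "adjusting for baseline nutrient profiling score and stratification factors" and then adds "A similar approach will be used for continuous secondary outcomes". No covariate list is given for expenditure. Apart from the general tabulation of baseline characteristics, no analytic use of family size is named. The section also says "A statistical analysis plan will be prepared by the trial statistician prior to the final data lock".

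**The concern.** The covariate set was written for a nutrient profiling score, which is an average over products and need not rise with the number of people fed. Carried over to expenditure, it is applied to a total that probably does rise with household size. The only term in the model that reflects household size would then be spend in one baseline week. That week includes week-to-week variation as well as the household's usual level, and eligibility requires only one supermarket shop a week. Family size relates to the usual level, so it carries information that one week of receipts does not fully supply.

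What is at stake is the width of the confidence interval for one secondary outcome, the one that shows whether an interpretive label changes what shoppers spend.

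**Working it through.** **1. The plan's own power figure.** It concerns the primary outcome only: 500 per arm, a 2-unit difference, SD 9.9, two-sided, two comparisons with control. The standardised difference is 2 / (9.9 × √(2/500)) = 2 / 0.626 = 3.194. With a Bonferroni level of 0.025 per comparison (my assumption for the multiplicity adjustment), power = Φ(3.194 − 2.241) = 83.0%, and 466 per arm would be needed for 80%. At 0.05 the power is 89.1%. Both agree with the stated minimum of 80%, and nothing below changes that figure. No SD, reliability or target difference is given for expenditure.

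**2. Model for expenditure.** Weekly spend = stable household level (variance B) + independent weekly variation (variance W). The outcome is the mean of 4 weeks and the baseline is 1 week, both from the article. Single-week reliability is B/(B + W). Family size explains a share s of B and is unrelated to the weekly variation. B, W and s are assumptions.

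- Residual variance with baseline spend only: V₀ = (B + W/4) − B²/(B + W).
- Residual variance with family size added: V₁ is the same expression with B replaced by B(1 − s).
- Standard-error ratio: √(V₁/V₀).

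**3. Middle case A** (B = 1, W = 1, reliability 0.5, s = 0.35):
- V₀ = 1.25 − 1/2 = 0.750.
- V₁ = (0.65 + 0.25) − 0.4225/1.65 = 0.644.
- V₁/V₀ = 0.859, so residual variance falls by 14.1% and the standard error by about 7% (√0.859 = 0.927). This is equivalent to about 16% more participants for this outcome (1/0.859 = 1.16).

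**4. Middle case B** (reliability 0.5, correlation of family size with usual spend 0.5, so s = 0.25): R² rises from 0.400 to 0.457. The residual variance ratio is 0.905 and the standard-error ratio 0.951, a cut of about 5%.

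**5. Range.**

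| Reliability | s | Variance ratio | Cut in standard error |
|---|---|---|---|
| 0.8 | 0.09 | 0.985 | about 1% |
| 0.67 (W = 0.5) | 0.20 | 0.944 | about 3% |
| 0.5 | 0.25 | 0.905 | about 5% |
| 0.5 | 0.35 | 0.859 | about 7% |
| 0.3 | 0.36 | 0.846 | about 8% |
| 0.33 (W = 2) | 0.50 | 0.771 | about 12% |

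If s is held to at most 0.36 (correlation 0.3 to 0.6), the cut is about 1% to 8%. Allowing s up to 0.50 takes the upper end to about 12%.

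**6. What the model omits.** The strata are not in the comparator. To the extent that ethnicity or interest in healthy eating predicts household size or spend, s should be read as the share left after the strata, which would shrink the gain.

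**The case against.** The strongest case against the point is that the article says nothing wrong here. Its sentence on secondary outcomes names a type of model and excludes no covariate. A condensed article ordinarily leaves the covariate list for one of nine secondary outcomes to the analysis plan. ANCOVA on the baseline value and strata is standard and, under randomisation, unbiased. Collecting a demographic item to describe the sample creates no duty to adjust for it. The run-in requires at least 15 recorded barcoded items, so near-empty baseline weeks are ruled out. Shoppers who do only half of the household's shopping may weaken the link between recorded spend and family size. Every input to the size of the gain is assumed.

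Most of this stands, and it limits the point to an improvement in efficiency. The item minimum ensures a usable baseline week, but it does not make one week a precise measure of usual spend, and the reliability range up to 0.8 allows for a good one. What remains is that a predictor of the outcome is already collected, the default model as described does not name it, and naming it in advance costs almost nothing.

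A reader might infer more, and the documents do not support it:

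- *That the plan rules family size out.* It does not. It leaves it unnamed, and the analysis plan could add it.
- *That the expenditure comparison is biased or confounded by household size.* Randomisation prevents systematic imbalance, so only precision is affected.
- *That a rise in household costs would be missed.* With no SD or target difference for expenditure, no power or loss of power can be computed.
- *That the income tertiles for the sub-group analysis should be corrected for family size.* The article does not say whether income is personal or household, so there is no basis for this.

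**Conclusion.** The point holds as a minor gain in efficiency. It is not an error in the plan. On the natural reading, expenditure is adjusted for one noisy baseline week and the two strata, and family size could add information. The likely gain is a standard error 5% to 7% smaller in middle cases, within roughly 1% to 12% over the assumed ranges. This rests on three things: spend behaves as a stable household level plus independent weekly variation; recorded spend scales with household size, which is inferred from the main-shopper criterion; and the strata take up little of what family size explains. If weekly spend is very stable and family size only weakly related to it, the gain is close to nil.

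**What to change.** In the Statistical analyses section, or in the analysis plan before data lock, state that the food-expenditure ANCOVA will include family size as an additional covariate alongside baseline expenditure and the stratification factors. State whether it enters as a number or in categories. Fix this before outcome data are examined, since adding it afterwards would look post hoc.

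The data are already collected, so participants bear no extra burden. The costs are one model term and, because the article plans no imputation, the loss from this analysis of anyone with family size missing. If values are missing at random across participants, the gain is cancelled when the missing fraction reaches 1 − V₁/V₀. That is about 9.5% in middle case B (1 − 0.905) and about 14% in middle case A (1 − 0.859), but only about 1.5% at the weakest end of the range (1 − 0.985). Completeness of the item should therefore be checked, blind to outcome, before the model is fixed.

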## Discussion

The aim of the Starlight RCT is to measure the effects of two interpretive FOP nutrition labels, compared with the standard NIP, on the healthiness of food purchases. To our knowledge, this is the first RCT assessing the impact of interpretive FOP labels on objectively measured consumer purchases in real-world retail outlets nationwide, without restriction to a particular store or setting. The unique smartphone app designed for the trial will allow shoppers to view nutrition labels of barcoded food products in any retail outlet. The randomised controlled design of the Starlight trial enables use of the NIP label at an individual level as a control, rather than using a control store. The advantage of this approach is that it minimises confounding effects of patterns of sales in different retailers. Another advantage is that it neutralises any effect of using the smartphone app to scan products. The “Food Label Trial” smartphone app will also allow objective assessment of nutrition label use when shopping since this information will be collected automatically by the app. The Starlight trial will also assess the impact, utility and acceptability of proposed label format for Māori and Pacific adults. This is of particular importance, considering the high prevalence of obesity and nutrition-related disease among those groups [9]. According to study by Signal et al. [8], self-reported use of nutrition labels is low among those groups, and both claim to favour simpler nutrition labels that are easier to understand. Whilst FOP labels are the focus of much government, industry and advocacy group attention worldwide, their impact on consumers’ behaviour is uncertain. This large, randomised, controlled trial will provide robust evidence of the effectiveness and potential cost-effectiveness of FOP labelling as means to improve population diets and health.

### Trial status

Recruiting.

## Abbreviations

FOP: Front-of-pack
NIP: Nutrition information panel
App: Application
TL: Traffic-light
HSR: Health star rating
RCT: Randomised controlled trial.
